### 2.7. Intervention

In all patient groups, a 120 cm 12 French gauge (1 French = 0.33 mm) nasally placed small-bowel feeding tube was standardized for use in the institution where the study will be carried out. The length of the tube needed to reach the jejunum will be assessed prior to insertion and measured by placing the nasally placed small-bowel feeding tube from the earlobe to the xiphoid process and then down to the umbilicus (EXU method).^[19]^ Before insertion, 3 milliliters of 2% xylocaine will be applied to the patient nostril, selecting the one with no nasal obstruction or deviated septum. In each group, the nasally placed small-bowel feeding tube will be passed through the patient nostril, posteriorly along the floor of the nose and advanced to reach the measured length.

### 2.8. Endpoint

#### 1.2.8. Primary outcome.

The success rate on the first attempt will be considered as the dependent variable. Insertion success will be defined as the successful passage of the tube on the first attempt and confirmed by radiography of the correct anatomical positioning of the tube distal tip, which will be performed immediately after the procedure. If the nasally placed small-bowel feeding tube is not successfully inserted, it will be considered a failure and recorded as an unsuccessful attempt. Subsequently, new attempts will be performed.

The number of attempts required for successful insertion will be recorded for each patient. It should be noted that if more than 3 attempts are required, the procedure will be declared unsuccessful and data will be used to count failures. In these cases, the researchers may use another method of free choice for nasally placed small-bowel feeding tube insertion.

#### 2.2.8. Secondary outcome.

Secondary endpoints will be time required and associated complications. The time required will be recorded from the nasally placed small-bowel feeding tube insertion from the nostril to the calculated length of the tube with the aid of a stopwatch. The insertion times for each attempt will be counted and, in case of failures, the time required for each attempt will be added together.

In addition, AEs associated with the insertion techniques (bleeding of the visible mucosa, nasal mucosa edema, in addition to tube bending, twisting, knotting and insertion into the trachea visible on X-ray) will be recorded. It is noteworthy that the occurrence of bleeding will be considered as visible bleeding in the tube extension and nasal or oral mucosa. The analysis of such AEs will be performed immediately at the end of the procedure until radiological confirmation of the tube positioning and previous removal of the guide wire. The radiograph will be performed on the patient bed and the patient will be kept in the same position, in the supine position. If the patient shows signs of respiratory distress during insertion, the procedure will be stopped.

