## Abstract

**Methods::**

A prospective, randomized and controlled clinical trial will be carried out with coma and intubated patients admitted to the Intensive Care Unit (ICU). Thirty-nine patients will be randomly divided into 3 groups: group who will have the tube inserted in a conventional manner with the head in the neutral position, group with the head positioned laterally to the right, and, finally, with the head in the neutral position, with assistance of a laryngoscope. The primary endpoint will be: first, second and total attempt success rate; and time required for the first successful attempt and the sum of all attempts. Complications during insertion included tube bending, twisting, knotting, mucosal bleeding, and insertion into the trachea. Patient vital signs will be measured.

Strengths and Limitations of this Study•This is a single-center study, and participants will be recruited from a single hospital, which compromises the generalisability of the findings;•Blinding of nurses will not be possible;•The instrument used did not go through the face and content validation process.

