### 2.10. Randomization and masking

Thirty-nine patients will be randomly divided into 3 groups. Patients allocated in the control group (CG) will have the tube inserted in the conventional way, that is, the head is kept in the neutral position, while the tube is gently inserted through one of the nostrils, without any maneuver or instrument.

Patients selected for the first intervention group (GI1) will have their heads turned to the right lateral position. This way, the tube will be inserted through the selected nostril without any neck maneuver or instrument.

For patients selected for the second intervention group (GI2), a conventional adult laryngoscope will be orally inserted. The tracheal tube and tongue will be raised to provide the best view of the larynx area. Thus, after viewing the piriform sinus or the esophagus, the tube will be inserted into the patient nostril and advanced to the esophagus under direct visualization. The patient head will be held in the neutral position and the blade will be gently lifted to avoid excessive neck extension.

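### The insertion-time clock starts at the nostril, so laryngoscopy in GI2 goes untimed and the measured time cannot show which technique is faster overall

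*Protocol article*

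**What the plan says.** The clock is defined in section 2.8 under Secondary outcome: "The time required will be recorded from the nasally placed small-bowel feeding tube insertion from the nostril to the calculated length of the tube". For repeated attempts, "in case of failures, the time required for each attempt will be added together".

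The order of steps by arm is in section 2.10:

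- **GI2 (laryngoscope):** first "a conventional adult laryngoscope will be orally inserted", then the tracheal tube and tongue are lifted for a view of the larynx. Only then, "after viewing the piriform sinus or the esophagus, the tube will be inserted into the patient nostril and advanced to the esophagus under direct visualization".
- **GI1 (lateral head):** patients "will have their heads turned to the right lateral position", and the tube follows.
- **Control:** the tube is passed with the head neutral, "without any maneuver or instrument".

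Section 2.7 describes preparation shared by all arms (length measurement, choice of nostril, local anaesthetic), all of it before insertion. The form described in section 2.11 has a single entry for time, in seconds.

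The endpoint's rank is not consistent. Section 2.8 makes time secondary, while the abstract lists "time required for the first successful attempt and the sum of all attempts" under the primary endpoint. Insertion time is also named in the null and alternative hypotheses in the Introduction.

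**The concern.** The stopwatch runs over the same physical interval in each arm, but that interval is a different share of each technique. In GI2 it leaves out the steps that distinguish laryngoscopy from blind insertion. In control it leaves out nothing that is particular to the arm. If the techniques took equally long overall, the measured times would still differ, in the direction of GI2.

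This matters because of how the result is to be used. The Introduction and the Discussion want to tell nurses which technique is, among other things, fast, and the Discussion speaks of streamlining work. Those are statements about the whole technique. A nostril-to-length time does not support them, and a later analysis cannot restore time that was never recorded.

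**Working it through.** The plan states no figure to reproduce. The check has two parts: the text, which settles the direction, and an illustration of scale.

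**1. What the clock leaves out, by arm**

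| Step | Control | GI1 | GI2 | Timed? |
|---|---|---|---|---|
| Measurement, nostril choice, anaesthetic (2.7) | yes | yes | yes | no, in any arm |
| Head turn (2.10) | – | yes | – | no |
| Blade insertion, lifting, viewing (2.10) | – | – | yes | no |
| Nostril to calculated length (2.8) | yes | yes | yes | yes |

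The shared preparation is untimed in all arms and drops out of the contrast. Write T for the time from the first arm-specific step to the calculated length, L for the arm-specific set-up, and M for the measured time. Then M = T − L, with L = 0 in control, L > 0 but probably small in GI1, and L > 0 in GI2. For mean times,

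measured difference (GI2 − control) = true difference − mean L in GI2.

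The sign is fixed by the text. The size is not, because the article gives no times, SDs or laryngoscopy durations.

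**2. Scale, under assumptions**

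Assumed: 13 patients per arm (39 / 3; section 2.9 is itself unclear on the split), equal true T in both arms, and a two-sided 5% two-sample t-test.

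*(a) Normal times, L as a multiple of the SD.* The noncentrality is (L/SD) × √(13 × 13 / 26) = (L/SD) × 2.55, with 24 degrees of freedom.

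| L/SD | Chance of a significant difference |
|---|---|
| 0.25 | 9% |
| 0.5 | 23% |
| 0.8 | 50% |
| 1 | 69% |

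*(b) Log-normal times, median 60 s, 20,000 simulated trials per cell.* GI2 measured time is a draw from the control distribution minus L.

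| Omitted L | log-SD 0.3 | log-SD 0.5 | log-SD 0.8 |
|---|---|---|---|
| 5 s | 10% | 6% | 4% |
| 10 s | 26% | 11% | 6% |
| 15 s | 50% | 20% | 9% |
| 20 s | 72% | 31% | 12% |

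At 10 s and above, nearly all of these results favour GI2. The two models agree. The SD of a log-normal is median × exp(s²/2) × √(exp(s²) − 1), where s is the log-SD. For s = 0.3 this is 60 × 1.046 × 0.307 = 19.3 s, so 15 s is 15 / 19.3 = 0.78 SD, and table (a) gives 50% at 0.8 SD.

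*(c) Where the model fails.* Subtracting a fixed L can give impossible negative times. The share below zero is Φ(ln(L/60)/s). At L = 30 s and s = 0.5 it is Φ(−0.693/0.5) = Φ(−1.386) = 8.3%, so 1 − (1 − 0.083)^13 = 68% of trials hold at least one. At L = 20 s and s = 0.8 it is Φ(−1.099/0.8) = 8.5%, again about 68% of trials. I therefore leave out 30 s, and the larger omissions at the wider SDs are rough.

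**The case against.** The best defence is that nostril-to-length is a coherent endpoint, defined identically in every arm, and that the hypotheses speak of insertion time without naming a direction. That much stands: tube-passage time is legitimate if it is labelled and interpreted as such. The difficulty is that the article calls it the time required and uses it, unrestricted, to look for the fast technique.

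A second defence is that an article condenses the protocol. Here, however, the start and stop of the clock are stated outright, so this is not a detail left to another document.

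Some stronger readings are tempting, but the article does not support them:

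- *A reader might infer that control is timed from start to finish.* It is not. The shared preparation in section 2.7 is untimed there too. Control merely lacks arm-specific set-up.
- *A reader might infer that the omission recurs at every attempt.* The article does not say whether the blade is withdrawn and re-inserted, or the head turned again, between attempts. If laryngoscopy is repeated, the omission accumulates in the summed time.
- *A reader might infer that both intervention arms gain alike.* GI1 has one head turn, probably short. In substance the point is about GI2.
- *A reader might infer a firm error rate, even above half.* The results depend wholly on assumed spread and set-up time, and the highest ones lean on impossible negative times.
- *A reader might infer that the trial's main result is compromised.* The body of the article makes first-attempt success primary, and it does not depend on the clock.

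**Conclusion.** The point holds for GI2. Followed exactly, the plan measures tube passage, and as a measure of how long the technique takes it is tilted towards the laryngoscope arm. The direction follows from sections 2.8 and 2.10 alone. The size cannot be derived from the article. Under the stated assumptions (13 v 13, equal total times, median 60 s, log-SD 0.3 to 0.8) a significant difference appears in about 4-10% of trials with 5 s omitted, 6-26% with 10 s, 9-50% with 15 s and 12-72% with 20 s. The effect may thus be negligible or large.

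Severity is moderate. Time is secondary in the body, and success and complications are untouched. It is not minor, because insertion time stands in the hypotheses, the abstract lists it under the primary endpoint, and unrecorded set-up time is lost for good.

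**What to change.** For all further patients, record for each attempt:

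- **Total procedure time:** from the first arm-specific step (start of the head turn in GI1, start of laryngoscope insertion in GI2, tube pick-up in control) to the calculated length.
- **Tube-passage time:** nostril to calculated length, as now, taken as a lap time and reported under that name.

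Base any statement about the faster technique on total procedure time. For patients already enrolled, report tube-passage time only, so labelled.

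The cost is one extra stopwatch press and one field on the form, with no change to how the tube is placed. The real downside is that section 2.1 says collection is under way, so total time will be missing for everyone enrolled before the change. The article does not say how many that is. If too few patients remain for a useful comparison, rename the endpoint tube-passage time and limit the hypothesis and conclusion to that. In either case, give time the same rank in the abstract and in section 2.8.

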### 2.4. Eligibility criteria

The study will include patients in physiological coma (score between 3 and 8 on the Glasgow Coma Scale) or induced coma (score between 5 and 6, slow response to stimuli and deep sedation, respectively), on the Ramsay scale, submitted to invasive mechanical ventilation, indication of nasoenteral tube under medical prescription, aged 18 years or older. It is noteworthy that patients who lost the nasoenteral tube due to inadvertent exit or obstruction will also be included.

Exclusion criteria were: patients with coagulopathy (abnormal prothrombin time, partial thromboplastin time and platelet disorders); nasal stenosis; upper respiratory tract anomalies; esophageal disorders (esophageal hiatus hernia, esophageal varices, esophageal or nasopharyngeal carcinoma); skull base fracture; teeth with mobility and history of difficult intubation. In order to verify such information, medical records were consulted before the procedure was performed.

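### The complication list omits dental, non-bleeding lip and tracheal-tube harms of the laryngoscope arm, and events of a later free-choice method have no attribution rule

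*Protocol article*

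**What the plan says.** All references are to the protocol article.

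- **Complications (2.8, Secondary outcome).** The list reads "AEs associated with the insertion techniques (bleeding of the visible mucosa, nasal mucosa edema, in addition to tube bending, twisting, knotting"; its last item is the feeding tube entering the trachea, as seen on X-ray. Bleeding is then defined: "the occurrence of bleeding will be considered as visible bleeding in the tube extension and nasal or oral mucosa". The abstract gives nearly the same list.
- **Timing (same section).** "The analysis of such AEs will be performed immediately at the end of the procedure until radiological confirmation of the tube positioning".
- **After failure (2.8, Primary outcome).** "if more than 3 attempts are required, the procedure will be declared unsuccessful and data will be used to count failures". In that case "the researchers may use another method of free choice for nasally placed small-bowel feeding tube insertion".
- **Laryngoscope arm (2.10).** The laryngoscope goes in through the mouth, and "The tracheal tube and tongue will be raised to provide the best view of the larynx area". The other two arms use no instrument.
- **Exclusions (2.4).** These include "teeth with mobility and history of difficult intubation".
- **Data collection (2.11).** The form records the technique, the number of attempts, the time and any complications. It also records heart rate, respiratory rate, blood pressure and oxygen saturation before, during and after insertion.
- **Aim (Introduction and Discussion).** The presence of complications is part of both the null and the alternative hypothesis, and the trial hopes to identify a safe technique.

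**The concern.** A comparison of complications between techniques is fair only if the endpoint can register the characteristic harms of each technique. Most of the listed events are those of passing a feeding tube through the nose: the tube bends, twists, knots or enters the trachea, or the mucosa bleeds or swells. The laryngoscope is meant to reduce several of these. What it adds is a blade in the mouth and movement of the tracheal tube, and the harms specific to that, apart from visible oral bleeding, are not listed.

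If the endpoint is tallied as written, GI2 is credited with any reduction in tube events but is not charged with a broken tooth, a bruised lip or a displaced tracheal tube. A statement at the end of the trial that one technique is safer would then rest on an incomplete count for one arm.

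A second, lesser question is what happens to events in patients who fail with the assigned technique and go on to another. The article does not say to which technique such events belong.

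**Working it through.** **1. The list set against the techniques.** The article gives no figure for this endpoint, so there is none to reproduce. The check is a comparison of sections.

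| Possible harm | Named in 2.8 or recorded in 2.11? |
|---|---|
| Visible bleeding, nasal or oral | Yes, listed |
| Nasal mucosa edema | Yes, listed |
| Tube bending, twisting, knotting | Yes, listed |
| Feeding tube in the trachea | Yes, listed |
| Fall in oxygen saturation | Recorded as a vital sign, not listed as a complication |
| Dental injury | Not listed |
| Lip injury without visible bleeding | Not listed |
| Displacement of the tracheal tube | Not listed |

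The last three rows belong above all to the arm described in 2.10 as using an oral blade and lifting the tracheal tube. Section 2.4 screens out patients with loose teeth or a difficult airway. That exclusion makes sense for laryngoscopy and suggests that the risk was in view when the protocol was written.

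**2. Size of one missed event.** Input: 13 per arm, taken as 39/3. Section 2.9 also gives 26 to each intervention group, which does not fit a total of 39, so both sizes are shown.

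- 13 per arm: 1/13 = 7.7 percentage points.
- 26 per arm: 1/26 = 3.8 percentage points.

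This applies to a GI2 patient who has an unlisted harm and no listed one. A patient who also bleeds visibly is already counted.

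**3. How often a missed event might arise.** The article gives no rate for these harms, so the rates below are assumptions. The chance of at least one in 13 patients is 1 − (1 − r)^13.

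| Assumed rate r | Chance of none in 13 | Chance of at least one |
|---|---|---|
| 1% | 0.878 | 12.2% |
| 5% | 0.513 | 48.7% |
| 10% | 0.254 | 74.6% |
| 20% | 0.055 | 94.5% |

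**4. Patients reaching the free-choice method.** Assume independent attempts with constant success probability p, and 13 per arm. The share failing three attempts is (1 − p)³. The value 82.7% is the first-attempt rate of a study cited in the Introduction; the other values are assumed.

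| p | (1 − p)³ | Expected in 13 | Chance of at least one |
|---|---|---|---|
| 0.827 | 0.5% | 0.07 | 6.5% |
| 0.70 | 2.7% | 0.35 | 30% |
| 0.50 | 12.5% | 1.6 | 82% |
| 0.40 | 21.6% | 2.8 | 96% |

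The attribution question is negligible at the cited rate. It matters only if success per attempt in an arm is much lower.

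**The case against.** Several parts of the case on the other side are sound.

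- **The list is not confined to nasal and tube events.** A reader might infer that it is. The bleeding definition includes the oral mucosa, so blade trauma that visibly bleeds is counted. The gap is dental injury, lip injury that does not bleed, and tracheal-tube displacement.
- **Some of this may be caught elsewhere.** The form has an open entry for complications next to the technique used, and oxygen saturation is recorded around each insertion. The full form is not shown. This softens the point but does not remove it: an open entry does not require anyone to look for a given harm, and saturation is not defined as part of the complication endpoint.
- **Exclusions lower the risk.** They do, but they do not make the harm impossible in those enrolled.
- **The recording window.** A reader might infer that it stays open through the free-choice method, so that its events are charged to the randomised arm. The text does not say so. The procedure is declared unsuccessful first, the events are those of the insertion techniques, and assessment starts at the end of the procedure, which may well mean the assigned one. Equally, the window ends at radiological confirmation of position, which in a failed patient may come only after the other method. The article is silent, and both readings are open.
- **Direction and size of the second issue.** A reader might go on to conclude that a sizeable part of the control arm's complications could belong to another method, and that this too favours GI2. That would need the open-window reading, more three-attempt failures in the control arm than elsewhere, and extra events from an unspecified method. None of these is shown. About three such patients in 13 would need a success rate per attempt near 40%, for which the article gives no support.

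**Conclusion.** The main point stands. The complication endpoint, as listed, leaves out dental injury, non-bleeding lip injury and tracheal-tube displacement, although one arm alone uses the instrument most likely to cause them. The comparison can therefore miss harms of GI2 and tend to favour it. Each missed patient is worth 7.7 points at 13 per arm (3.8 at 26). How many there would be is unknown; the rates used above are assumptions.

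The attribution of events after a switch of method is a secondary clarification. Its expected size is about 0.07 patients per arm at the cited 82.7%, assuming independent attempts, and its direction is not established.

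Neither point touches the primary outcome, first-attempt success. Both bear on any claim about safety.

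**What to change.** 1. Add to the listed complications, in all three arms, dental or lip injury (bleeding or not) and tracheal-tube displacement or accidental extubation. Looking for them in every arm keeps ascertainment equal.
2. Report between arms the oxygen saturation already recorded before, during and after insertion. No new measurement is needed.
3. Record for each event the technique in use. Count in the randomised comparison only events up to the end of the last attempt with the assigned technique, and list later events separately.

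The cost is a few items and one column on the form, with no change to treatment. The real drawback is that data collection is already under way (2.1). Patients enrolled before the change must be reported as not assessed for the added items, not as free of them, so the comparison on those items will rest on fewer patients. The added items may also make GI2 look less favourable, which is a proper result of a complete count.

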## 1. Introduction

According to the World Health Organization, 1 in 10 patients experience unnecessary harm as a consequence of unsafe health care assistance, which in more extreme situations, can cause the patient death.^[1]^ In this context, patient safety is related to a set of activities that aim to mitigate risks to an acceptable minimum, make the error less likely and, when it occurs, reduce the impact^[2]^ prevents the occurrence of adverse events (AEs) or injuries resulting from health procedures.^[3]^

In this context, despite being a common procedure, nasally placed small-bowel feeding tube insertion is not risk-free and can compromise patient safety. Due to the fact that nasally placed small-bowel feeding tube is commonly inserted ‘“blindly,” with the patient head in the neutral position, sometimes the process becomes difficult and traumatic, and may present higher level of complexity in physiological or induced coma and intubated patients, as the tongue displaced backwards blocks the passage through the pharynx. In addition, the piriform sinus and the arytenoid cartilage are considered anatomical obstacles for the nasally placed small-bowel feeding tube passage, which is sometimes bended in the oral cavity due to the inability to swallow and the presence of the endotracheal cannula cuff.^[4]^

Therefore, AEs such as accidental tube displacement, wrong positioning in the respiratory tract, tube obstruction, inadvertent exit, bronchoaspiration and connection route errors can occur during this procedure.^[5,6]^ Among serious and fatal AEs, pneumothorax, aspiration pneumonia and pulmonary hemorrhage stand out.^[7,8]^

There are different nasally placed small-bowel feeding tube insertion methods in critically ill and/or coma patients, which, although less common, have high procedural success rates, but none of them is perfect or universally accepted.^[9,10]^ It is noteworthy that the choice of techniques for this study was based on high success rate, low cost, availability and the lack of need to remove the patient from the Intensive Care Unit (ICU).^[11–14]^

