Results favorable to the use of different nasally placed small-bowel feeding tube insertion methods have been described by anesthesiologists.^[11–13]^ Among these, the lateralized head^[5,12]^ and the use of the laryngoscope^[11]^ stand out. Such studies have demonstrated nasally placed small-bowel feeding tube insertion methods that are faster, more effective and that cause less complications to patients. However, it is clear that such techniques are little used by nurses in clinical practice. It is important and necessary for nurses to be able to offer safer care with less risk of complications, based on the best available evidence, through the possibility of revealing the most adequate, effective, fast and safe technique to improve the execution of this procedure.

In a study conducted in Taiwan, 130 insertion attempts were performed. The success rate was 82.7% (86 of 104 patients) on the first attempt and 100% in 5 attempts. In 23 patients the tube deviated to the oral cavity and 3 to the trachea.^[15]^ Verification of vital signs are important to detect clinical deterioration of the patient.^[16]^

We seek to test the following hypothesis: null hypothesis: There are no significant differences between the methods of insertion of the nasally placed small-bowel feeding tube in patients in coma (physiological or induced) and intubated in relation to the rate of success in the first attempt, insertion time and the presence of complications; alternative hypothesis: There are significant differences between the methods of nasally placed small-bowel feeding tube insertion in comatose patients (physiological or induced) and intubated in relation to the rate of success in the first attempt, insertion time and the presence of complications.

Therefore, the study aims to determine the effectiveness of different nasally placed small-bowel feeding tube insertion techniques in coma and intubated patients, in comparison with conventional method.

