### 2.11. Data collection

A data collection printed form containing variables about patients will be used, namely: Identification (bed; name initials; age; sex; date of birth); Clinical data (cause of admission; estimated weight, height and body mass index); Level of consciousness or Ramsay scale data, including type of drug used and sedation duration; Endotracheal tube number and cuff pressure; Data regarding the technique used (technique; number of attempts; required time in seconds; complications, if any); Parameters to be evaluated (heart and respiratory rate, blood pressure and oxygen saturation) before, during and after nasally placed small-bowel feeding tube insertion using each of the techniques; Confirmation of the correct nasally placed small-bowel feeding tube positioning by chest and abdomen radiography in bed.

Table 1 shows the detailed study stages, with the Standard Protocol Items for Randomized Trials schedule of enrollment, interventions, and assessments.

**Table 1 T1:** Description of the study stages: P1: Day 1—request for nasally placed small-bowel feeding tube insertion in the patient and intervention. F1: evaluation after the procedure until X-ray is performed.

Study period					
			Post-allocation: Allocation, interventions, follow-up		
Timepoint	Enrollment	Baseline	Allocation	P1 intervention	Follow-up (F1)
Enrollment:					
Eligibility criteria	X				
Recruitment	X				
Initial assessment	X				
Informed consent	X				
Allocation			X		
Interventions:					
Insertion in a conventional manner (control group)				⟷	X
Insertion with the head turned to the right side (intervention group)				⟷	X
Insertion with laryngoscope (intervention group)				⟷	X
Assessments:					
Identification, clinical data, level of consciousness, SSVV, among others		X			

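### Tube bending, twisting and knotting are tied to an X-ray named only as chest and abdomen, so bends in the mouth may go uncounted as complications, and detection may differ by arm

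*Protocol article*

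**What the plan says.** Five places in the protocol article bear on this point.

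- **Definition of the complication (2.8, Secondary outcome).** After visible bleeding and nasal oedema, the list continues "in addition to tube bending, twisting, knotting and insertion into the trachea visible on X-ray) will be recorded". Adverse events are assessed from the end of the procedure until radiological confirmation. Bleeding is looked for along the tube and on the nasal or oral mucosa, in every arm.
- **The film (2.11).** The data form includes "Confirmation of the correct nasally placed small-bowel feeding tube positioning by chest and abdomen radiography in bed". No other radiographic field is named.
- **Where tubes go wrong (Introduction).** Of the tube, the article says "which is sometimes bended in the oral cavity due to the inability to swallow". Of a cited series of 104 patients and 130 attempts it says "In 23 patients the tube deviated to the oral cavity and 3 to the trachea".
- **What the operator can see (2.10).** In GI2, "the tube will be inserted into the patient nostril and advanced to the esophagus under direct visualization". In the control group the head stays neutral "while the tube is gently inserted through one of the nostrils, without any maneuver or instrument". In GI1, "the tube will be inserted through the selected nostril without any neck maneuver or instrument".
- **Primary outcome (2.8).** Success needs radiographic confirmation that the distal tip is correctly placed. Otherwise the attempt is recorded as unsuccessful.

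**The concern.** The article names the mouth as a place where the tube bends, then ties bending to a film that is not described as covering the mouth. A bend, twist or knot above the upper edge of that film would not meet the definition as written, even if someone at the bedside could see it.

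The arms also differ in what can be seen while the tube is passed. A direct view during insertion belongs to GI2 alone. If what the operator sees can be entered as a complication, the three arms do not have the same means of detecting it.

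Complications are a secondary endpoint and part of the stated hypothesis. The data form is completed and the X-ray read by the collaborating researcher who also handles randomization (2.6), and only the data analysts are blinded. Masking therefore does not protect this endpoint, and a clear common definition has to do that work.

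**Working it through.** The plan states no figure for this point, so the check is mainly a comparison of sections. The cited series gives some limited arithmetic.

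**Step 1. The two readings of the sentence in 2.8.**

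| Reading | Oral bend counted? | Same method in all arms? |
|---|---|---|
| A. The X-ray phrase qualifies all four tube events | Only if the film reaches the mouth | Yes, so the risk is under-counting in every arm |
| B. The X-ray phrase qualifies tracheal insertion only | Not stated; no method is given | Not secured, because GI2 alone has a view during insertion |

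A is the natural reading. The Abstract lists the same complications without mentioning a film, which leaves B open. Each reading has a defect, but a different one. Under-counting by X-ray belongs to A, and unequal detection belongs to B.

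**Step 2. Direction under B.** No rule says whether a bend seen through the laryngoscope is recorded, or whether one seen and corrected at once is recorded. If both are, GI2's count rises relative to the other arms. If corrected bends are left out, it falls. The direction is not fixed.

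**Step 3. What the cited series shows.** Inputs, all from the Introduction: 104 patients, 130 attempts, 86 first-attempt successes, success in all patients within five attempts, 23 oral deviations, 3 tracheal.

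- Failed attempts: 130 − 104 = 26.
- Deviations: 23 + 3 = 26, an exact match.
- Patients who failed a first attempt: 104 − 86 = 18.

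If the deviations are the failed attempts, as the match suggests, they come from at most 18 patients. They are best read as events, although the article words them as patients. Oral share: 23/26 = 88%. Tracheal share: 3/26 = 12%. The mouth is the main site of deviation in that series.

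**Step 4. What happens to an oral deviation under this plan.** If the distal tip is not correctly placed, the attempt is a failure under 2.8 and is recorded as one. What can be lost is its record as a complication. A tube that loops in the mouth with its tip correctly placed would count as a success and might not be recorded as a complication at all. The documents give no frequency for that case.

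**Step 5. Scale, as illustration only.** Assume 39/3 = 13 patients per arm and the cited event count per patient, 23/104 = 0.22. Expected oral events per arm = 13 × 23/104 = 2.9. If an assumed half are detected, 1.4 are recorded; if a quarter, 0.7. The detection fractions are not from the documents. The cited series allowed up to five attempts and this trial allows three, so 2.9 may be too high. With so few events, one or two missed in one arm could create or hide a difference.

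**The case against.** Several objections have force.

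- **The mouth is already examined in every arm.** The oral mucosa is checked for bleeding in all three groups, in a window that opens before the film. This stands: a reader might infer that only GI2 looks in the mouth, and that is wrong. Only the view during insertion is unique to GI2. But the common check is stated for bleeding, not for the course of the tube.
- **The two biases need opposite readings.** This stands too. Under reading A the definition is the same in all arms; under reading B bending is not tied to the film. They cannot both be asserted as fact.
- **The upper limit of the film is inferred.** True. It is inferred from the film's name, and section 2.11 describes it for confirming position. Nothing in the article says that it reaches the mouth.
- **The 88% is not the share of complications missed.** Correct, though tempting to infer. Deviation into the mouth is not the same event as bending, twisting or knotting, and most such events would be recorded as failed attempts.
- **Detail may lie in the scripts and printed form, which are not shown.** Possibly. But the article does not merely leave the method out: it states a method in the definition, and that is what needs changing.
- **Restricting the comparison to a common method drops real events from GI2.** Fair. Those events should therefore be reported as well.

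**Conclusion.** The point holds as a risk to one secondary endpoint. As written, bends in the mouth or pharynx may go uncounted as complications, or, on the other reading, have no stated method of detection and may be detected unequally by arm. The primary outcome is largely protected by the tip check.

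The size is unknown. The cited series shows only that the mouth was the main site of deviation (23 of 26 events). The conclusion rests on two assumptions: that a chest and abdomen film does not reliably show the mouth, and that the check of the oral mucosa for bleeding is not also a check of the tube.

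A reader might go further and conclude that the control group and GI1 will look falsely safe beside GI2. The documents do not support that. No rule says whether laryngoscope sightings are recorded, so the difference could run either way or not arise.

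**What to change.** In section 2.8 and on the data form:

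1. Count bending, twisting or knotting if seen on a bedside look at the mouth and oropharynx at the end of each attempt, done the same way in all three arms alongside the existing oral mucosa check, **or** if seen on X-ray.
2. State whether the X-ray phrase governs all four tube events or tracheal insertion only.
3. Record the source of each event: bedside look, X-ray or laryngoscope view.
4. Compare the arms on events found by the common method (bedside look or X-ray). Also report events seen only through the laryngoscope, so that they are not lost.
5. Record the date of the change and how many patients were assessed before it, since section 2.1 says that data collection is under way. An oral bend that was not looked for cannot be recovered later.

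The cost is a brief added check at each attempt and one form field, with no extra staff or procedure. The recorded complication rate may rise, and patients enrolled before the change will have been assessed under the old rule, which the report should state.
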